# 7.- SAFETY ASSESSMENT

Safety assessments will be carried out in accordance with Good Clinical Practice guidelines and current legislation.

The sponsor is responsible for managing the adverse events (AEs) recorded during this study. The sponsor is responsible for the expedited reporting of suspected unexpected serious adverse reactions (SUSARs), annual reports or any other relevant safety information to the health authorities (AEMPS, CCAA) and clinical research ethics committees (CRECs).

The sponsor is also responsible for reporting safety information to the investigators.

- Definitions. Classifications.

Adverse event (AE):

Any incident that is harmful to the health of the patient or clinical trial subject treated with a medicinal product, even if it does not necessarily have a causal relationship with said treatment.

An AE may therefore be any unfavourable and unintentional sign (including an abnormal laboratory finding), symptom, or disease temporally associated with the use of an investigational medicinal product, whether or not considered related to the medicinal product.

Adverse Reaction (AR):

Any unintended harmful reaction to an investigational medicinal product, regardless of the dose administered.

In contrast to an AE, in the case of an AR there is a suspected causal relationship between the investigational medicinal product and the adverse event.

All AEs and ARs will be classified as mild, moderate or severe based on their severity.

Severity Criteria

The severity will be defined as specified below:

- Mild: the patient experiences discomfort that does not interfere with their daily activity.
- Moderate: sufficient discomfort to reduce or affect daily activity.
- Severe: inability to work or undertake daily activity.

Causality criteria

The sponsor will classify adverse events based on their causality relationship with the drug, as per the Karsch and Lasagna algorithm (1977), as:

- - - Definitive: there is a reasonable time sequence between administration of the drug and onset of the adverse event. Said event coincides with the adverse reactions described for the drug, improves upon suspension thereof, reappears after re-administration and cannot be explained by other causes.
    - Probable: there is a reasonable time sequence between administration of the drug and onset of the adverse event. Said event coincides with the adverse reactions described for the drug, improves upon suspension of treatment and cannot be explained by other causes.
    - Possible: there is a reasonable time sequence between administration of the drug and onset of the adverse event. Said event coincides with the adverse reactions described for the drug but may be explained by other causes.
    - Conditional or improbable: there is a reasonable time sequence between administration of the drug and onset of the adverse event. Said event does not coincide with the adverse reactions described for the drug and can be explained by other causes.
    - Unrelated: there is no reasonable time sequence between administration of the drug and onset of the adverse event. Said event does not coincide with the adverse reactions described for the drug and can be explained by other causes.

For the purposes of expedited reporting, the categories definitive, probable and possible from the Karsch and Lasagna algorithm (1977) will be considered to be related and the category conditional or improbable will be considered to be unrelated.

The principal investigator at the research site, or a person designated by the PI, will be responsible for determining the possible relationship with the study treatment.

Serious Adverse Event (SAE) and Serious Adverse Reaction (SAR)

Any adverse reaction or adverse event which, at any dose:

- - - Causes the death of the patient.
    - Endangers the patient’s life.
    - Requires hospitalisation or prolongation of hospitalization of the patient.
    - Causes permanent or significant disability or incapacity.
    - Leads to a congenital anomaly/birth defect.

For reporting purposes, those suspected adverse events or adverse reactions considered to be important from a medical point of view will be considered to be serious even if they fail to comply with the above criteria, including important medical events requiring an intervention to prevent any of the consequences described above from occurring. Similarly, all suspected transmissions of an infectious agent via a drug will be reported as serious. The concept “serious”, defined above, should not be confused with “severe”, which refers to the severity of the AE or AR (mild/moderate/severe).

Suspected Unexpected Serious Adverse Reaction (SUSAR)

Any adverse reaction whose nature or severity does not correspond with the reference information for the product (for example, the Investigator's Brochure in the case of an investigational medicinal product that is not authorised for marketing, or the summary of product characteristics for the product if it is an authorised drug).

The unexpected nature of an adverse reaction is based on the fact that it has not been observed previously and will not be based on what might be expected given the pharmacological properties of the drug.

SAEs that do not comply with the SUSAR criteria and which are associated with blinded studied will be reported to the health authorities unblinded.

Management of adverse events/pregnancy

Recording of adverse events/pregnancy

All adverse events/pregnancies notified either spontaneously by the patient or during the interviews held during the study visits will be recorded. AEs/pregnancies will be recorded from the moment the patient signs the informed consent (IC) up until 30 days after administration of the last dose of the investigational medicinal product and/or final visit.

In the event of pregnancy, the patient will be excluded from the study.

Information concerning the AEs that may have occurred in the period of time between the previous visit and the current visit must be requested.

All AEs/pregnancies must be documented in the patient’s medical records and the case report form (CRF).

All AEs must be followed up until they have resolved, or for at least 30 days after withdrawal of the study drugs (whichever occurs first), until the toxicity returns to a grade ≤ 1, or until the toxicity is considered to be irreversible.

Any pregnancy that occurs during the study, and its outcome, must be recorded and followed-up to rule out congenital malformations or birth defects. The following information should be recorded:

- Normal birth, miscarriage or abortion (any congenital abnormality detected in the aborted foetus must be documented), stillbirth, congenital abnormality.
- Neonatal deaths occurring in the first 30 days after birth.
- Death of an infant subsequent to those 30 days if the investigator suspects this to be related to intrauterine exposure to the study drug.
- All infants born after foetal exposure must be followed-up for the first 12 months after birth.

Any exacerbation of a pre-existing disease that occurs subsequent to start of the study treatment is also considered to be an adverse event.

Any abnormal finding in blood tests that the investigator considers to be clinically significant and which requires adjustment of the dose of study drug, temporary or permanent suspension of said treatment or any type of intervention of diagnostic evaluation to evaluate the associated risk for the patient should be recorded as an adverse event and should be investigated and monitored accordingly.

Procedure for notifying SAEs/pregnancy to the sponsor

If an SAE that must be notified to the Clinical Trials Unit occurs, or a pregnancy is recorded, a member of the research team will complete and sign an SAE or pregnancy notification form, which will be sent to the Clinical Trials Unit immediately and always within 24 hours of becoming aware of the event.

The form received will be reviewed and, if applicable, additional information will be requested from the investigator.

When additional Information concerning the SAE/pregnancy is obtained, or it resolves or is unlikely to undergo any change, a follow-up report must also be completed and sent to the Clinical Trials Unit.

If the SAE is suspected to be a SUSAR, the investigator must provide the follow-up information requested by the Clinical Trials Unit.

Any SAE that occurs more than 30 days after the completion of treatment (with no time limit) must be reported if the investigator considers that the SAE is related to the study treatment (in other words, if it is a serious adverse reaction) or if it is medically important.

Expedited reporting of SUSARs to health authorities/CREC

The Clinical Trials Unit is responsible for notifying the AEMPS (clinical trials division of the Sub-Directorate General for Medicines for Human Use), CRECs and autonomous communities of all SUSARs recorded during the study as per the procedure set out in current legislation.

Reporting periods

The maximum period for reporting an individual case of a SUSAR is 15 calendar days from the moment when the sponsor becomes aware of said event. If the SUSAR has led to the death of a patient, or endangered the patient’s life, the sponsor will send the information within a period of 7 calendar days from the moment they become aware of said event. This information will be completed, as far as possible, within the next 8 days.

# 8.- STATISTICS

## 8.1.- Sample Size

The expected number of infusions is 48, distributed into 16 infusions per group. It is recommended to include between 30 and 50 measurements in a pilot study^18,19^.

## 8.2.- Statistical analysis

A general description of all study variables will be performed. Qualitative variables will be expressed as absolute frequencies and percentages, and quantitative variables as the mean and standard deviation (median and 25th and 75th percentiles if they do not follow a normal distribution). The primary endpoint will be evaluated using a chi-squared test (with a Fisher correction if it does not comply with the criteria) and the secondary endpoints will be evaluated by performing a chi-squared test (with a Fisher correction if they do not comply with the criteria) for categorical variables, and Student’s t-test (or Mann–Whitney U-test if they do not follow a normal distribution) will be applied for continuous variables. A Kaplan Meier survival analysis will be applied to determine the time to the infusion-related reaction. A statistical significance level of p<0.05 will be used in all tests. Statistical analysis will be performed using the statistical software packages R (version 3.5.0) and SPSS (version 23.0).

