# 3.- AIM AND PURPOSE OF THE STUDY

## 3.1. Hypothesis

Increasing the infusion rate for rituximab is as safe as administration under standard practice (400 mg/h).

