# 4.- TRIAL DESIGN

**4.1.- Variables**

Primary variable:

-Percentage of grade 2/3 or higher infusion-related reactions for the rapid, ultrarapid and ultrarapid plus infusions in comparison with the administration of rituximab as per standard clinical practice at the standard rate of 400 mg/h.

** Infusion-related reactions are defined as adverse events that occur in the first 24 hours after infusion of rituximab and which are considered to be related to infusion of the drug in the investigator's opinion.*

Secondary variables:

- Grade of infusion-related reactions (1-5 as per CTCAE version 4.0) occurring in each study group.

- Time (in minutes) between the start of infusion and onset of the infusion-related reaction.

Other variables:

- Age (years)

- Sex (male/female)

- Infusion group (rapid, ultrarapid or ultrarapid plus)

- Treatment type (induction/maintenance)

- Therapy type (rituximab in monotherapy/combination therapy - specify the type of concomitant treatment: chemotherapy, radiotherapy, targeted therapy, etc.)

- Lymphoma type (specify diagnosis)

- Rituximab cycle number

- Blood pressure, temperature, oxygen saturation and heart rate before starting and after finishing rituximab infusion

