# 5.- SUBJECT SCREENING AND WITHDRAWAL

Inclusion criteria:

- Patients who have tolerated the maximum intravenous administration rate for rituximab (400 mg/h) during the first or second infusion.
- The last infusion of rituximab must have taken place in the previous 3 months.
- All patients receiving rituximab may be included irrespective of whether they do so as monotherapy or in combination with chemotherapy and irrespective of the line in which they are receiving it.
- Patient in both induction and maintenance treatment will be included.
- All patients must sign the informed consent.

Exclusion criteria:

- Patients with an initial absolute lymphocyte count >10x10^3^ cells/µL.
- Patients who have presented hypersensitivity and serious adverse effects (grade 2 or higher) after the first or second infusion.
- Severe heart failure (NYHA class III-IV) or severe uncontrolled heart disease.
- Respiratory failure, uncontrolled COPD/severe asthma.
- Patients allergic to the premedication: paracetamol or polaramine.
- Severe active infection.
- Pregnant patients. *
- Refusal to participate

* For patients of child-bearing age (women of child-bearing age are considered to be those between menarche and post-menopause, except for those who are permanently sterile), a pregnancy test must be performed prior to treatment.

Women of child-bearing age participating in the trial must use effective contraceptive methods during treatment and for up to 12 months afterwards. These methods include:

- - - Sexual abstinence.
    - Female sterilisation.
    - Sterilisation of the (male) partner.
    - Intra-uterine device (IUD)

Withdrawal criteria:

- Onset of one or more grade 2 or higher infusion-related reactions
- The presence of four or more mild to moderate infusion-related reactions (25%) in the 16 patients of the corresponding cohort

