# 6.- SUBJECT TREATMENT

When the patient attends the haematology surgery and has tolerated the maximum intravenous administration rate for rituximab (400 mg/h) during the first or second infusion, they will be invited to participate in the study and will be given the informed consent. If the patient complies with all the inclusion criteria and none of the exclusion criteria, and decides to participate, they will be given an appointment to attend the day hospital for administration of their treatment cycle at the infusion rate being studied at that time.

Three successive intervention groups with different infusion rates (rapid, ultrarapid and ultrarapid plus) will be established. The procedure for each cohort will be considered to be safe if fewer than four mild to moderate infusion-related reactions occur in the 16 patients from the corresponding cohort (25% of reactions). The onset of one or more grade 2 or higher infusion-related reactions will imply that the cohort is not safe and the clinical trial will be suspended. Before commencing the next cohort, a haematology specialist not linked to Araba University Hospital Haematology Department will carry out a safety monitoring. This will involve an evaluation of all infusions performed, with access to the progress reports (medical and nursing) to determine whether a reaction has occurred and the grade thereof. In an attempt to minimise the influence of the investigator on the safety evaluation, the safety monitor will receive the progress reports after references to the grade of the infusion-related reaction contained in the electronic medical records have been censored.

Rituximab will be diluted in 250 mL provided the maximum concentration established in the summary of product characteristics (max. 4 mg/mL) is not exceeded. The rituximab dose will not be changed.

If the patient is receiving concomitant chemotherapy, this will be administered after rituximab once the absence of adverse reactions has been confirmed.

The interventions applied in each of the three study groups are described below:

RAPID INFUSION GROUP

Administration of the IV premedication half an hour prior to the infusion of rituximab as per the standard regimen; generally, dexchlorpheniramine 5 mg IV and paracetamol 1 g IV half an hour prior to rituximab.

The rituximab dose will then be administered at the standard dose: 375 mg/m^2^ diluted in 250 mL of saline over one hour, as follows:

- - - First 10 minutes at 450 mg/hour

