    - Subsequent 50 minutes at 720 mg/hour

A total of 16 infusions will be included in this group and the safety thereof will be evaluated. If the number of AEs is not higher than normal (more than three infusion-related reactions), the second intervention will commence. In the event that the number of infusion-related reactions is higher than in standard clinical practice, the study will be suspended without continuing with the following groups.

ULTRARAPID INFUSION GROUP

Administration of the IV premedication half an hour prior to the infusion of rituximab as per the standard regimen; generally, dexchlorpheniramine 5 mg IV and paracetamol 1 g IV half an hour prior to rituximab.

The rituximab dose will then be administered at the standard dose: 375 mg/m^2^ diluted in 250 mL of saline over half an hour, as follows:

- - - First 10 minutes at 450 mg/hour.
    - Subsequent 20 minutes at 1800 mg/hour.

A total of 16 infusions will be included in this group and the safety thereof will be evaluated. If the number of infusion-related reactions is not higher than normal (more than three infusion-related reactions), the third intervention will commence. In the event that the number of infusion-related reactions is higher than in standard clinical practice, the study will be suspended without continuing with the following group.

ULTRARAPID PLUS INFUSION GROUP

Administration of the oral premedication half an hour prior to the infusion of rituximab as per the standard regimen for administration of subcutaneous rituximab: dexchlorpheniramine 4 mg orally and paracetamol 1 g orally half an hour prior to rituximab.

The rituximab dose will then be administered at the standard dose: 375 mg/m^2^ diluted in 250 mL of saline over half an hour, as follows:

- - - First 10 minutes at 450 mg/hour.
    - Subsequent 20 minutes at 1800 mg/hour.

A total of 16 infusions will be included in this group and the safety thereof will be evaluated. This ultrarapid infusion regimen will be considered to be safe if the number of infusion-related reactions is three or less.

Safety will be evaluated by monitoring infusion-related reactions, including all haematological and non-haematological serious and non-serious adverse events related to the study drugs. If an infusion-related reaction occurs, the standard administration rate of 400 mg/h will be used.

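### The primary chi-squared/Fisher test cannot support the equal-safety hypothesis: no margin and no 400 mg/h data are defined, and under the one-event suspension rule cohorts have almost no events to compare

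*Protocol*

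**What the plan says.** - **Hypothesis (Protocol 3.1):** "Increasing the infusion rate for rituximab is as safe as administration under standard practice (400 mg/h". No margin is attached.
- **Primary variable (4.1; 3.2.1 is equivalent):** "Percentage of grade 2/3 or higher infusion-related reactions for the rapid, ultrarapid and ultrarapid plus infusions", to be set against standard practice at 400 mg/h. The infusion groups to be recorded are the three study groups only.
- **Primary analysis (8.2):** "The primary endpoint will be evaluated using a chi-squared test (with a Fisher correction if it does not comply with the criteria". All tests use p<0.05; sidedness is not stated.
- **Suspension (6):** "one or more grade 2 or higher infusion-related reactions will imply that the cohort is not safe and the clinical trial will be suspended". Section 5 lists the same event as a withdrawal criterion: "Onset of one or more grade 2 or higher infusion-related reactions".
- **Other rules for calling a cohort safe (6):** a cohort passes if "fewer than four mild to moderate infusion-related reactions occur in the 16 patients from the corresponding cohort". The ultrarapid plus regimen "will be considered to be safe if the number of infusion-related reactions is three or less", with no grade given, and the two earlier cohorts have a similar ungraded limit.
- **Power (4.5):** the protocol concedes that the sample is too small to show significant differences from 400 mg/h. It keeps both the hypothesis and the test.

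**The concern.** The hypothesis claims equal safety, but the test looks for a difference. Failing to find one is not evidence of equality, least of all with 16 infusions per cohort.

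The primary event is also the event that suspends the trial. The threshold in the primary variable can be read as grade 2 or as grade 3, but on either reading the event falls inside the suspension rule. If that rule governs, a cohort that completes and is followed by another has no primary events, which leaves a between-cohort test almost nothing to work on.

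The likely report is therefore an undefined or non-significant p-value beside the word *safe*. Section 4.5 presents this pilot as the step before a multicentre trial. Whoever plans that trial needs the highest reaction rate still compatible with the data, and Section 8.2 does not make that the primary result.

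**Working it through.** **The plan's own figures.** 3 × 16 = 48 infusions and 4/16 = 25%; both reproduce. The 48 comes from a rule of thumb for pilot studies (8.1), so there is no alpha, power or effect size to reproduce.

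**Step 1: between-cohort tables under the one-event rule.** Assume a two-sided test and suspension at the first event. An event in the first cohort leaves no second cohort to compare. Otherwise one event occurs at infusion k of the current cohort, against 0 of m earlier infusions. With a single event, Fisher's two-sided p is k/(k+m) when k<m, and 1.0 when k=m.

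| Situation | Table | Result |
|---|---|---|
| All cohorts clean | 0/16, 0/16, 0/16 | Chi-squared undefined (expected counts of zero); Fisher p = 1.0 |
| Event at last infusion of cohort 2 | 1/16 v 0/16 | p = 1.0 |
| Event at first infusion of cohort 2 | 1/1 v 0/16 | 1/17 = 0.059 |
| Event at first infusion of cohort 3 | 1/1 v 0/32 | 1/33 = 0.030 |
| Event at second infusion of cohort 3 | 1/2 v 0/32 | 2/34 = 0.059 |

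Only an event at the very first infusion of cohort 3 gives p<0.05.

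**Step 2: comparison with an external 400 mg/h series.** The protocol defines no such series, so the sizes and counts here are assumptions.

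- Clean cohort: 0/16 v 10/200, p = 1.0; v 20/200, p = 0.37; v 40/200, p = 0.047. The only significant result points towards fewer reactions at the faster rate.
- One event: 1/16 v 0/200, p = 16/216 = 0.074; v 0/500, p = 16/516 = 0.031.

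The answer depends on a series that is not specified. Non-significance would still not show equal safety. In the 10/200 example p is 1.0, yet 0/16 is compatible with a rate of 20.6%, about four times the assumed 5% (20.6/5 = 4.1).

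**Step 3: what a clean cohort shows.**

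- Two-sided 95% upper limit: 1 − 0.025^(1/16) = 20.6%.
- One-sided 95% upper limit: 1 − 0.05^(1/16) = 17.1%.
- Probability of a clean cohort, (1−p)^16: 0.44 at a true rate of 5%, 0.185 at 10%, 0.028 at 20%.

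**Step 4: the wording that tolerates up to three reactions.** The grading table in 3.2.1 labels grade II as moderate. A limit that counts moderate reactions therefore admits primary events that the one-event rule forbids.

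- If only this wording applied, 3/16 has an exact 95% interval of 4.0% to 45.6%.
- P(X ≤ 3 | n = 16) is 0.93 at a true rate of 10%, 0.60 at 20% and 0.40 at 25%, the protocol's own limit.
- Some significant tables then become possible: 3/16 v 0/32 gives C(16,3)/C(48,3) = 560/17,296 = 0.032.

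**Step 5: size of a formal comparison, for scale.** Assume equal true rates p, one-sided 0.025 and 80% power. Then n per arm = 2p(1−p)(1.960+0.842)²/margin².

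- p = 5%, 10-point margin: 2 × 0.0475 × 7.85/0.01 = 74.6, so 75.
- p = 10%, 5-point margin: 2 × 0.09 × 7.85/0.0025 = 565.2, so 566.

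**The case against.** **The named comparison is with 400 mg/h, not between cohorts.** This is correct, and it limits the point. A reader might infer that the primary test is empty and its non-significance fixed in advance. The documents do not support that. Against an external series with events the test is computable, and against a large clean series one event could be significant (Step 2). A clean series is not far-fetched: Section 2.1 reports no significant complications at 400 mg/h under the local practice begun in 2010. What stands is that no such series is defined and that a difference test without a margin cannot show equal safety in any case.

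**Zero events by rule rests on one of several conflicting rules.** This is also correct. Under the wording that tolerates up to three reactions, a passing cohort could hold grade II events. The zero is conditional on the one-event rule.

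**Several events might accrue before suspension.** They might, if grading is settled only at the independent review between cohorts. Against one clean cohort it would take 5/16 v 0/16 to reach significance (p=0.043); against two, 3/16 v 0/32 is enough (p=0.032).

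**Section 4.5 admits low power, and an analysis plan may exist.** The admission concerns sample size. It softens the criticism but leaves in place a test that does not address the hypothesis. Section 8.2 states the primary test outright, so this is not a detail left for later.

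**The trial would say nothing about safety.** That inference is too strong. A clean cohort bounds the rate at about 21%; it is not a comparison with standard practice.

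**Conclusion.** The concern holds in this form: the primary test in Section 8.2 does not match the hypothesis in 3.1, and its result, significant or not, could not establish equal safety. If the one-event rule governs and suspension is immediate, between-cohort tests are undefined or non-significant in every case but one. Any comparison with 400 mg/h depends on data that the protocol does not define, and a clean cohort could only point towards fewer reactions.

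The attainable precision is an upper limit of 20.6% for 0/16, or an interval of 4.0% to 45.6% for 3/16. Both assume independent infusions and a completed cohort of 16. They are approximate if a patient contributes more than one infusion to a cohort, or if the cohort stops early. Section 6 speaks of 16 patients in one place and 16 infusions in others, so the first possibility is open.

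This should be fixed. It affects what the pilot may claim, but the protocol is open about its low power and no change to the trial's conduct is required.

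**What to change.** 1. **Section 8.2.** Make the primary analysis the per-cohort proportion of reactions of grade 2 or above, with an exact (Clopper-Pearson) 95% confidence interval, and report any-grade reactions the same way. Drop the significance test as evidence of safety, and treat any comparison with 400 mg/h as descriptive.
2. **Sections 3.1, 3.2.1 and 4.1.** Restate the aim and primary variable as estimation, so that endpoint and analysis agree.
3. **Section 6.** Word a favourable outcome as *criterion to proceed met* rather than safe.
4. **Precision.** State the attainable limits (0/16: 20.6%, one-sided 17.1%; 3/16: 4.0% to 45.6%) and the assumptions behind them.
5. **Sections 5 and 6.** Reconcile the one-event rule with the limits that tolerate up to three reactions. Which rule applies is for the trial's clinicians to decide.

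No extra patients are needed. The change is more than cosmetic, because it turns a comparative objective into an estimation objective. The cost is a less favourable claim: even a clean cohort excludes only rates above about 21%. Keeping a formal claim of equal safety would need a margin and a defined comparator, on the scale of 75 to 566 per arm under the assumptions in the working. That belongs in the planned multicentre trial.
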